#### Survey on knowledge and attitudes on DVA

Subscale scores from BRAVE survey will be calculated. For each participant change scores will be calculated between baseline and follow-up score. Generalized Estimating Equations analysis will be used to compare mean change score in the intervention and control teams. The CMH team will be included as a random effect to account for the clustering of the data. Questionnaires with more than 5% of the questions missing will be removed from the sample. Questionnaires with less than 5% missing will be imputed using multiple imputation.

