#### Secondary aims and outcomes

The BRAVE intervention has the following secondary aims and outcomes:

Aim 1 - to assess gains and sustainability in knowledge on DVA among mental health professionals.

Aim 2 - to assess the feasibility, sustainability and acceptance of the intervention among CMH teams and,

Aim 3 - to assess the (possible) referral pathway to DVA services and the implementation of the Meldcode.

We will assess Aim 1 using a structured questionnaire – The BRAVE Survey - developed specifically by the study team, to assess CMH teams knowledge and attitudes regarding DVA.

Aim 1 - the BRAVE survey

The BRAVE survey was informed by the PREMIS [37] and PROTECT questionnaires [38].

All members of the included teams will receive this survey. The survey has a total of 53 questions divided into 5 sections: (1) Respondent profile, (2) Previous Courses on DVA (3) Skills in management of DVA, (4) Knowledge on DVA and (5) Opinions on DVA. Section 1; “Respondent profile” consists of 7 questions, of which 3 are multiple choice and 4 questions an individual can fill in. Participants are asked about their professional background (work experience, current profession, educational level) and general information (date, age, gender); section 2; “Previous courses attended on DVA” consists of a multiple choice question about previous courses on DVA. If participants check yes they are asked 4 questions about duration of this course and when this course was completed. Section 3; “Skills in management of DVA” consists out of 7 multiple choice statements. Participants can check the box on the Likert scales, ranging from 1 (not skilled) to 5 (very skilled), the extent to which they feel skilled to handle/judge a particular described situation regarding DVA. Section 4; “Knowledge on DVA” consists of a total of 14 multiple choice statements. For the first three questions, participants need to check the box on Likert scales, ranging from 1 (nothing) to 5 (a lot). These questions are followed by 10 multiple choice questions with statements about DVA where participants can choose between true (1) and not true (2). The last question in this section asks the participants to combine the correct described statement with the right stage of the process of discontinuing a relationship with a perpetrator. Section 5; “Opinions on DVA” consists of 16 statements on DVA where participants can choose whether they agree on a Likert scale ranging from 1 (do not agree) to 5 (agree).

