To be able to compare the scores of the survey, sections 3 (Skills), 4 (Knowledge) and 5 (Opinions) will be calculated separately per participant and will then be aggregated at a team level. Qualitative answers will be given a score and, post-hoc assigned to answering categories. Statistical comparisons will be made between intervention and control teams.

This questionnaire will be assessed at baseline, after 6 months of the intervention and after 12 months of the intervention.

We will assess Aim 2 by conducting semi structured in-depth interviews with members of CMH teams, policy makers, patients and DVA practitioners about the feasibility, sustainability and acceptance of the intervention.

Aim 2 Semi-structured in depth interviews

We will obtain outcomes regarding opinions on feasibility, sustainability and acceptance of the intervention using a semi-structured in depth interview with a purposive sample of professionals in the intervention - and control group, team-leaders, managers, patients in the intervention group, patients in the control group, patients who have experienced DVA and patients who didn’t experience DVA. The interview for clinicians will mostly focus on their opinions and personal definition of the following themes:DVAactions (not) takenreferral pathways between CMH services and DVA servicesimpact of the intervention on care provision and care professionals (including personal safety)impact of the intervention on client relationshipimpact of the intervention on client wellbeing (including personal safety)level of implementation of the intervention in daily practicefeasibility of implementation of the interventionsustainability of the intervention

In the policy makers of the included mental health institution and team managers the in depth interview will focus on their opinions and personal definition of the following themes:DVAthe interventionreferral pathways between CMH and DVA serviceslevel of collaboration between CMH and DVA servicesimpact of the intervention on care provision and operational capabilitycost-effectiveness of the intervention

The in depth interview with psychiatric patients will focus on their opinions and personal definition of the following themes:DVAdisclosure of DVAavailable help for DVA

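### The 5% rule counts unscored survey items and can discard complete subscale scores; the unit of analysis is stated in two ways, and change scores give up precision

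*Protocol article*

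**What the plan says.** All statements are in the protocol article.

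- **Missing items** (Statistical methods, Survey on knowledge and attitudes on DVA): "Questionnaires with more than 5% of the questions missing will be removed from the sample". Below that limit, "Questionnaires with less than 5% missing will be imputed using multiple imputation".
- **Survey length** (Secondary aims and outcomes): "The survey has a total of 53 questions divided into 5 sections". Section 1, the respondent profile, "consists of 7 questions, of which 3 are multiple choice". Section 2 "consists of a multiple choice question about previous courses on DVA", and then "If participants check yes they are asked 4 questions about duration of this course and when this course was completed". Sections 3, 4 and 5 have 7, 14 and 16 items.
- **Scoring and unit** (Secondary aims and outcomes): only skills, knowledge and opinions (sections 3 to 5) are scored. These scores "will be calculated separately per participant and will then be aggregated at a team level", and intervention teams are then compared with control teams.
- **Analysis** (Survey on knowledge and attitudes on DVA): "For each participant change scores will be calculated between baseline and follow-up score". Mean change is compared by generalized estimating equations, with team entered to account for clustering. The survey is taken at baseline, 6 and 12 months; which of the later waves supplies the follow-up score is not stated.

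**The concern.** The deletion rule is fixed in the text, and its denominator is not the set of items that enter the outcome. A respondent who leaves three profile items blank but answers all 37 scored items would be dropped, although nothing needed for the subscale scores is missing. A change score needs two questionnaires, so one deleted form costs the pair. Imputation is then reserved for the forms that need it least.

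The survey also contains four questions that some respondents are never asked, and the rule does not say how these count.

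Finally, the two descriptions of the analysis are not the same. One compares team aggregates; the other models individual change with clustering. They use different data and have different precision. At stake are the size and make-up of the sample for Aim 1, and precision that the baseline survey could supply at no extra data collection.

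**Working it through.** **1. The stated question count.** Sections 1 to 5: 7 + (1 + 4) + 7 + 14 + 16 = 49, where section 4 is 3 + 10 + 1 = 14. The stated 53 is not reproduced. Without the four conditional items the sum is 45. The scored sections alone give 7 + 14 + 16 = 37.

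**2. The deletion threshold.**

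| Denominator | 5% of it | 2 blanks | 3 blanks | Blanks that remove a form |
|---|---|---|---|---|
| 53 (stated) | 2.65 | 3.8% | 5.7% | 3 |
| 49 (summed) | 2.45 | 4.1% | 6.1% | 3 |

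The count mismatch does not move the threshold. On either count, imputation applies only to forms with one or two blanks. Unscored items number 7 + 1 + 4 = 12, so three blanks among them can remove a form whose 37 scored items are complete.

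**3. How many forms this could cost.** The article gives no item non-response rate. As an illustration only, assume blanks are independent across 53 items and across waves. P(more than 2 blanks) is then 9.0% at 2% non-response and 21.2% at 3%. For a baseline/follow-up pair, 1 − (1 − 0.090)² = 17.2% and 1 − (1 − 0.212)² = 38.0% (unrounded probabilities used). If blanks cluster in a few respondents, these figures do not hold.

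**4. The conditional items.** If the four unasked questions counted as missing, a respondent with no previous course would have 4/53 = 7.5% (or 4/49 = 8.2%) missing and be removed. If they count as not applicable, they remove nobody. Under the first reading, let p be the share of staff with a previous course (not given; assumed 20% to 80%). In the change-score analysis, staff answering no at baseline lose their baseline form in both arms, before any training; staff answering yes at baseline remain yes. The loss is 1 − p in each arm: 80% at p = 20%, 20% at p = 80%. It is equal by arm, but it leaves only staff with earlier courses.

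**5. Change score against baseline adjustment.** Assume equal variance σ² at both times and correlation r, ignoring clustering. The change-score variance is 2σ²(1 − r); the baseline-adjusted variance is σ²(1 − r²). The ratio is (1 − r²) / [2(1 − r)] = (1 + r)/2.

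| r | Adjusted / change-score variance |
|---|---|
| 0.3 | 0.65 |
| 0.5 | 0.75 |
| 0.7 | 0.85 |

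**6. The unit.** After aggregation there is one value per team and wave, so 24 values per wave, and no within-team clustering is left to model. The participant change-score model needs the individual values. One plan cannot be both as the main analysis.

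**The case against.** The strongest case on the other side is that a question not asked is ordinarily not applicable, and item coding is detail an article may leave to a fuller document. That stands: nothing in the article codes unasked questions as missing, so it cannot be said that the rule removes these respondents.

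A reader might go further and infer that deletion would differ by arm, because trained staff could report a course at follow-up while controls could not. Taking the follow-up form alone, with p = 40% and 80% attendance (both assumed), removal would be 1 − 0.40 = 60% in control and 0.60 × 0.20 = 12% in intervention. The documents do not support this. It needs unasked items coded as missing, section 2 answered afresh at follow-up, the trial's own training reported as a previous course, and shares that are not given. It also disappears in the change-score analysis, where step 4 shows equal loss by arm.

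A reader might also infer that a team-level comparison is underpowered. The Sample size section speaks only of a large effect, with no effect size and no unit, so no power can be derived from it.

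Change scores are legitimate in a randomized trial; the loss is of precision, not validity. Aggregation might be meant for description only, though the article does not say so. The stage-matching item in section 4 may have several parts, which could explain the count of 53. None of this answers the point that blanks in unscored items can delete complete scored sections.

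**Conclusion.** The point holds as a defect in how a secondary analysis is fixed, and it should be corrected.

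- **Deletion rule:** as written, three blanks anywhere remove a form although 12 of the 49 itemised questions are unscored. This follows from the text without assumptions. The number of forms lost cannot be derived; the 9% to 21% per wave is illustrative.
- **Conditional items:** an ambiguity, not an established error. It matters because the consequence ranges from no loss to the loss of every respondent without a previous course.
- **Unit:** the two descriptions conflict and must be reconciled.
- **Change scores:** valid but less precise; the adjusted variance is 0.65 to 0.85 of theirs for r = 0.3 to 0.7, assuming equal variances.
- **53 against 49:** a discrepancy to correct, with no effect on the threshold.

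A bias between arms is not shown, and the primary outcome is not affected.

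**What to change.** 1. Apply the missing-item rule only to the 37 scored items, section by section, and state that unasked questions are not applicable.
2. Impute missing scored items, or use all observed scores, instead of deleting whole forms. The 5% cut-off should not simply be carried over to sections: one blank is 1/7 = 14.3%, 1/14 = 7.1% or 1/16 = 6.3%, so a single blank would already exceed it in each.
3. Name one main analysis: a participant-level model of the 6- and 12-month scores, adjusted for baseline score and the socio-economic stratification factor, clustered by team, with a small-sample correction for 24 clusters. Label team aggregates as descriptive if they are kept.
4. Correct the question count, or explain how 53 is reached.

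The cost is a few sentences and slightly more analysis work. No further data are needed.

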### Fidelity scale

Fidelity of the BRAVE intervention will be assessed by an independent researcher during the intervention at the time points of 6 and 12 months. A fidelity scale will assess whether 5 key components of the intervention are in place 1) training for mental health professionals on DVA, 2) training for DVA practitioners on mental health, 3) identification of the components of DVA in routine mental health care, 4) Integrated DVA referral and care pathway 5) collaboration between DVA specialists and mental health professionals. The fidelity scale was developed in collaboration with the LARA research group.

### Data monitoring

This is a low risk study, a full data monitoring committee is not deemed necessary. A monitor and data archiving plan is in place.

### Assessment schedule

All teams eligible for participation will be included before the start of the intervention. After inclusion, teams will be assigned randomly to the control condition and intervention condition. All teams will receive a baseline assessment, an assessment at 6 months and an assessment at 12 months using the BRAVE survey. The number of detected cases of DVA will be studied over a 1 year period. The in-depth interviews will be conducted in the last period of the intervention period and after the intervention period (Table 1).

**Table 1 Tab1:**
[figure not shown]
An overview of activities during the study period

## Discussion

DVA is a problem worldwide and particularly vulnerable groups, such as psychiatric patients with severe mental illness, become victims of DVA while at the same time DVA often remains undetected in this group by mental health professionals. In this protocol, we will measure the efficacy of an intervention to improve knowledge and skill training for professionals about DVA and mental illness, as well as to implement a referral pathway between CMH and DVA services for DVA victims with mental illness. According to these premises, we underline the importance of this intervention for psychiatric patients suffering from DVA.

This study is the first cluster randomized controlled trial targeting both male and female psychiatric patients who potentially experience DVA, using an intervention that involves a training of mental health and DVA services, and the focus on the implementation of a referral protocol. Among victims of DVA, loss to follow up is considered a risk. MacMillan et al. [34] reported 42% loss over an 18 months follow up period. This high percentage loss is partly due to the nature of the problem studied. Victims of DVA show a high level of mobility and might be at high risk for subsequent violence after disclosure of the DV. By assessing our primary outcomes at team level, we minimize biases caused by individual drop out.

Furthermore, by randomizing teams we avoid contamination of skills and techniques of professionals in the intervention condition to the professionals in the control condition. However, since a cluster RCT is less precise than an individual trail, the chance of failing to detect a true intervention effect might increase (type II error). Also, the number of clusters in this trail is relatively small (i.e. 24 clusters), therefore randomization might partly fail, which would cause the patients in the control and intervention condition to differ from each other [39].

We do not foresee many risks in the attainment of this study. However, possible risks could occur if the mental health institutions discontinue facilitation of the CMH teams or reorganize the team structure, for instance by merging existing teams during the study period. This will affect the number, size and composition of clusters. This might lead to contamination and decrease of power. Also, municipal reorganization of the DVA services might affect the attainment of this study.

With better detection rates of DVA, the focus of research on this topic could shift towards improvement of treatment, prevention and interventions on DVA on an individual level.

## Abbreviations

BRAVE: Better reduction through assessment of violence and evaluation
CMH: Community mental health
DVA: Domestic Violence and Abuse
FACT: Functional assertive community treatment
ICC: Intraclass Correlation
IF: Inflation factor
IRIS: Identification and Referral to Improve Safety
LARA: Linking Abuse and Recovery through Advocacy
MEC: Medical Ethical Committee
RCT: Randomized controlled trial
SMI: Severe mental illness
VT: Veilig Thuis
